## Abstract

Introduction: Obesity is associated with severe asthma, but no specific treatment has been established. The gut microbiome is increasingly recognized as a crucial factor, but specific treatments focused on the gut microbiome have not been established. Recently, azithromycin has been found to have the capacity to attenuate exacerbations, a characteristic of severe asthma. The effect of azithromycin on obesity-induced severe asthma is not understood. Methods: The purpose of the present study is to clarify the effect of azithromycin on exacerbations in asthmatic patients with obesity. To explore the mechanism, the gut microbiome, metabolites of microbes such as short-chain fatty acids, and blood inflammatory cytokines will be analyzed to evaluate the correlation with the effect of azithromycin on exacerbations in obesity-induced severe asthma. A multi-center, prospective, single-arm intervention study is planned. Discussion: The present study will allow us to evaluate the effect of azithromycin on exacerbations, particularly in asthma patients with obesity, and explore biomarkers, targeting molecules including the gut microbiome, which are correlated with decreased exacerbations. The present results could contribute to identifying new therapeutic prospects and targeted microbes or molecules associated with severe clinical characteristics in asthmatic patients with obesity. Trial registration: This study has been registered as a prospective study with the University Hospital Medical Information Network (UMIN0000484389) and the Japan Registry of Clinical Trials (jRCTs071220023).

## 1. Introduction

Asthma is a common disease, and the majority of patients are well-controlled by treatment, including inhaled corticosteroids and bronchodilators, which are pivotal treatments for asthma [1,2]. However, approximately 5 to 10% of the patients are resistant to the standard treatments, and they are considered to have severe asthma [3]. Clinical phenotypes of severe asthma are heterogeneous, but recognized as symptomatic, with reduced pulmonary function, higher airway inflammation, and frequent exacerbations [4,5]. Exacerbation is one of the important events in severe asthma that is related to higher mortality, emergency hospital visits, increased medical costs, and lower quality of life [6,7,8]. Thus, better control exacerbations by treatment, along with exploring the severity mechanisms, are increasingly required. Recently, several biologics targeting molecules associated with eosinophilic inflammation such as interleukin (IL)-4, IL-5, IL-13, and immunoglobulin (Ig) E, called type 2 cytokines, have become available, and they have the capacity to provide control for some patients with severe asthma, especially those characterized by eosinophilic airway inflammation [9,10]. However, their efficacy is insufficient for patients with less or non-type 2 inflammation [11]. For such severe asthma patients without eosinophilic airway inflammation, exploring novel treatments and therapeutic targets is needed.

There is increasing evidence that overweight and obesity are associated with the severity of asthma. For example, overweight increases the asthma exacerbation rate [12], and obesity reduces the efficacy of the standard treatments including corticosteroids [13,14,15]. In addition, obesity accounts for approximately 60% of the general severe asthma population in the United States, which indicates that obesity is a major phenotype of severe asthma [16]. Unfortunately, this form of asthma does not have any specific and effective treatment other than weight reduction. Indeed, previous reports showed that diet- and/or exercise-induced weight loss improved asthma control, lung function, and asthma-related quality of life [17,18,19]. As mechanisms, decreased exhaled nitric oxide and improved allergic airway inflammation through regulatory T-cell function and neutrophilic inflammation were considered [19,20,21]. Because asthma with obesity includes more patients with clinical characteristics of less or non-eosinophilic inflammation than lean asthma [22], it is necessary to clarify the severity mechanisms of obesity-induced severe asthma as a treatment target and identify effective treatments focused on less eosinophilic inflammation.

The gut microbiome is recognized as essential in the severity mechanisms of obesity-induced asthma [23]. For example, specific microbes in the gut, especially the level of *Akkermansia muciniphila*, were found to be correlated with severity in obese asthmatic patients [24], and we also showed that the gut microbiome directly affected obesity-induced exacerbations of non-eosinophilic airway inflammation and airway hyper-responsiveness in vivo [25]. In addition, specific interventions for the gut microbiome, including prebiotics and antibiotics, attenuate exacerbations [25,26,27,28], indicating that the gut microbiome is a pivotal mechanistic target for obesity-induced severe asthma. In terms of the severity mechanisms via the gut microbiome, several studies focusing especially on body weight reduction by bariatric surgery, including Roux-en-Y gastric bypass and sleeve gastrectomy, as effective treatment for obesity-induced asthma have been reported [29]. For example, researchers have shown that bariatric surgery improved asthma control and airway hyper-responsiveness [30,31,32]. Importantly, bariatric surgery also has the capacity to change gut microbiome composition, including *Akkermansia muciniphila* and others [33,34,35]. Recently, the AMAZES study, a randomized, double-blinded, placebo-controlled trial, showed that azithromycin, which is one of the macrolide antibiotics, significantly reduced asthma exacerbations, and, importantly, the effects were significant for patients whether or not their inflammation status was eosinophilic [36]. Notably, azithromycin also has the capacity to alter the human gut microbiome [37] and attenuate airway inflammation in vivo through gut microbiome manipulation [38]. These data suggest that azithromycin has the possibility to reduce exacerbations of obesity-induced severe asthma with alterations of the gut microbiome, even though the clinical phenotype is mainly less or non-eosinophilic inflammation.

The present study is a multi-center, prospective, single-arm intervention study involving treatment with azithromycin for 48 weeks to clarify whether such treatment reduces exacerbations of obesity-induced severe asthma. To explore the mechanism, the gut microbiome, metabolites produced by microbes such as short-chain fatty acids, and blood inflammatory cytokines will be assessed to evaluate their correlation with the reduction in exacerbations by azithromycin in obesity-induced severe asthma. Importantly, the present study is designed as a single-arm intervention considering the gut microbiome and biomarker diversity of individuals, which allows us to avoid individual diversity at baseline and explore specific microbes and biomarkers associated with clinical outcomes with a relatively small sample size, taking into account ethical concerns. Compared to the AMAZES study mentioned above, the study design, participants, intervention dose of azithromycin, and study endpoints are largely different. Briefly, the present study is planned as a single-arm intervention study compared to a randomized, double-blinded, placebo-controlled trial in the AMAZES study because of the sample size calculation considering gut microbiome diversity of individuals set as secondary endpoints. As study participants, the present study targets Japanese asthmatic patients with obesity (BMI > 25 kg/m^2^) compared to asthma patients recruited in Australia and New Zealand regardless of their BMI in the AMAZES study. Considering efficacy and safety, the intervention dose of azithromycin is 250 mg per day in the present study compared to 500 mg, 3 times per week in the AMAZES study. Finally, the present study focuses on the gut microbiome and its metabolism as study endpoints. The present results will contribute to developing new therapies for obesity-induced severe asthma and identify targeted microbes or molecules associated with the regulation of asthma with obesity.

## 2. Materials and Methods

### 2.1. Study and Setting

The present study is a multi-center, open-label, prospective, single-arm intervention study. The duration of the intervention is 48 weeks. All patients with asthma are to be diagnosed by an expert pulmonary physician referring to the Global Initiative for Asthma (GINA) guidelines [39]. Briefly, the patients show asthma-related symptoms such as cough, sputum, shortness of breath, and/or wheezes, and clinical improvement, including the symptoms and/or forced expiratory volume in 1 s at more than 200 mL or 12% by treatment for asthma, including short-acting beta 2 agonists (SABAs) and inhaled corticosteroids. The body mass index (BMI) is calculated as the body mass divided by the square of the height (kg/m^2^). Obesity is defined as a BMI greater than 25 kg/m^2^, referring to the Japanese criterion [40]. In the present study, to focus on the effect of azithromycin on exacerbations in obesity-induced asthma patients, patients who have experienced one or more episodes of moderate or severe exacerbation in the previous year will be recruited according to the sample size calculation. Moderate exacerbations are defined as events that require a temporary or a permanent increase in the dose of inhaled corticosteroid, administration of antibiotics considering exacerbation of asthma-related symptoms, increased use of SABA for 2 or more consecutive days, and emergency visits related to asthma exacerbations without administration of systemic corticosteroids, referring to previous reports [36]. Severe exacerbations are defined as events that require administration of more than 10 mg of prednisolone for 3 consecutive days, hospitalization associated with the asthma exacerbation, and emergency visits related to asthma exacerbations with systemic corticosteroid administration, referring to previous reports [36]. The azithromycin regimen is 250 mg daily for 48 weeks, based on previous reports. Briefly, 48 weeks of azithromycin 500 mg, 3 times per week, showed a significant attenuating effect for exacerbations of asthma, but with 35% of patients experiencing diarrhea and 7% of patients stopping treatment due to severe adverse effects [36]. Another trial showed that 24 weeks of azithromycin 250 mg, 3 times per week, showed no significant effect on exacerbations of asthma compared to placebo [41]. In terms of adverse effects, the blood concentration of azithromycin 250 mg daily was significantly lower, with less adverse effects, including digestive disturbance and hearing disorder, compared to 500 mg, 3 times per week [42]. In addition, Japanese patients with non-tuberculosis mycobacteria who were administered azithromycin 250 mg daily for more than 1 year, which is approved by Japanese medical insurance, did not experience adverse effects other than skin rash in 3.2% [43,44]. According to these data, azithromycin 250 mg daily for 48 weeks was selected considering efficacy, safety, and standardization related to seasonal changes.

The present study was designed as a single-arm intervention considering the gut microbiome diversity of individuals. The composition of the gut microbiome differs depending on individual eating habits, medical history, and environmental factors [45,46,47], which suggests that exploring specific microbes associated with clinical outcomes would be difficult when comparing placebo and intervention groups. Therefore, the gut microbiome along with other biomarkers will be compared before and after intervention in a single-arm intervention, which allows us to avoid individual diversity at baseline. As concomitant drugs, corticosteroids and antibiotics other than macrolide antibiotics are allowed to treat exacerbations and/or infections at baseline and during participation in the present study. Antacid and anti-diarrheal agents are also allowed for ethical reasons, especially considering the adverse effects of azithromycin.

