### 2.3. Exclusion Criteria

Exclusion criteria are the following: aspartate aminotransferase or alanine aminotransferase greater than 100 IU/L; creatinine above 2.0 mg/dL; life-threatening arrhythmia or paroxysmal tachycardia with heart rate greater than 100 beats per minute; admitted for acute myocardial infarction or heart failure in the previous year; malignancy diagnosed in the previous 5 years, except for complete remission after treatment; macrolide antibiotic treatment in the previous 4 weeks; biologics including omalizumab, mepolizumab, benralizumab, and dupilumab in the previous 8 weeks at the start of azithromycin in the present study; QT interval requires correction for heart rate at more than 480 ms; pregnancy or breastfeeding; BMI less than 25 kg/m^2^; and ineligible for the present study as determined by the researchers.

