### 2.4. Study Endpoints

The primary endpoint is reduction in the exacerbation rate after 48-week treatment with azithromycin compared to that before the intervention (Table 1). The asthma exacerbation rate is defined as the proportion of analyzed cases with asthma exacerbations after treatment. Secondary endpoints are differences in clinical and laboratory parameters between before and after azithromycin treatment, including the blood eosinophil ratio, eosinophil count, IgE, pulmonary functions such as vital capacity (VC), forced vital capacity (FVC), %VC, forced expiratory volume in one second (FEV_1_), FEV_1_%, and %FEV_1_, and weight, BMI, level of fractional exhaled nitric oxide (FeNO), and scores on the asthma control test. Other secondary endpoints are to clarify the characteristics of the frequency of asthma exacerbations in improving/non-improving patients, and the diversity indices of the gut microbiome including the Chao 1, Shannon, and Simpson indices. For other exploratory endpoints, height, weight, BMI, and the tendency for decreased exacerbations will be assessed at 24 weeks of azithromycin treatment. In addition, biomarkers including cytokines, chemokines, short-chain fatty acids, metabolomics, and species of the gut microbiome will be compared between before and after azithromycin treatment and examined for relationships between changes and exacerbation at 48 weeks. The effects of sex and age attenuating the effect of azithromycin on exacerbations will also be assessed, because sex and age have been shown to have great impacts on the incidence and pathophysiology of asthma and obesity [26,48,49,50].

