### 2.5. Clinical Data to Be Collected, including Adverse Events

The present study consists of 7 visits: before intervention, at azithromycin initiation, 4 weeks later, 12 weeks later, 24 weeks later, 36 weeks later, and 48 weeks later. Informed consent will be obtained at visit 1 with recording of clinical information including treatment contexts for asthma, smoking index, exacerbation times in the previous year, and comorbidities. Physical measurements, electrocardiogram, and blood examination will be evaluated at all visits except for visit 1 to monitor adverse effects of azithromycin. Pulmonary function testing, FeNO, and asthma control tests are to be performed at visits 2, 5, and 7. Biomarker analyses of blood, including multiplex assay of cytokines and chemokines (Eve Technologies, Calgary, AB, Canada), short-chain fatty acids, and metabolomics analysis (Kyusyu Pro Search, Fukuoka, Japan) are to be performed at visit 2 and visit 7. Gut microbiome analysis with 16s rRNA Sequencing (Massachusetts Host-Microbiome Center at the Brigham and Women’s Hospital, Boston, MA, USA) will be performed at visit 1 and visit 7. In terms of adverse effects of azithromycin, if the participants have any symptoms, physical and laboratory abnormalities of grade 2 level associated with azithromycin, the dose will be reduced to 250 mg 3 times per week. If the participants have any symptoms, physical and laboratory abnormalities of grade 3 level associated with azithromycin, administration of azithromycin will be terminated immediately.

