### 2.8. Statistical Analysis

The primary and secondary endpoints and safety will be assessed in all patients completing 48 weeks of treatment. Then, patients without necessary exacerbation data for analysis or who withdrew consent before treatment will be excluded. For the primary endpoint, the asthma exacerbation rate at 48 weeks and its two-sided 95% confidence interval (CI) will be estimated with the normal approximation. The asthma exacerbation rate difference between pre- and post-treatment will also be tested binomially. For the clinical laboratory parameters and the diversity indices of the gut microbiome at pre-treatment and post-treatment as secondary endpoints, paired *t*-tests or McNemar’s tests will be used. The chi-squared test will be used to investigate the characteristics related to the frequency of asthma exacerbations. For other exploratory endpoints, height, weight, BMI, and tendency for an attenuation of the exacerbation rate at 24 weeks will be assessed by paired *t*-tests. Univariate analysis and multivariate analysis with a logistic regression model, adjusting BMI and body weight, will be performed to evaluate the relationships between the changes (improvement or no improvement in biomarker changes) and asthma exacerbation at 48 weeks.

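### Treatment of exacerbations can by itself create the exploratory association between microbiome or biomarker change and exacerbation, and the stated model has no term for it

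*Protocol article*

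**What the plan says.** **Outcome definition (protocol article, 2.1).** One way to meet the moderate definition is "administration of antibiotics considering exacerbation of asthma-related symptoms". The severe definition includes "events that require administration of more than 10 mg of prednisolone for 3 consecutive days". Other routes need neither drug: extra SABA use, a higher inhaled steroid dose, or an emergency visit without systemic steroids.

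**Permitted treatment (2.1).** The article states that "corticosteroids and antibiotics other than macrolide antibiotics are allowed to treat exacerbations and/or infections at baseline and during participation in the present study". The only antibiotic-free period among the eligibility rules concerns macrolides: "macrolide antibiotic treatment in the previous 4 weeks" (2.3).

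**Sampling (2.5, Table 1).** Stool analysis "will be performed at visit 1 and visit 7"; the blood biomarkers, including short-chain fatty acids, "are to be performed at visit 2 and visit 7". No interval between a treatment course and a sample is given.

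**Analysis (2.4, 2.8).** Biomarkers and gut species are to be "examined for relationships between changes and exacerbation at 48 weeks", as an exploratory endpoint. Univariate and logistic models are meant to "evaluate the relationships between the changes (improvement or no improvement in biomarker changes) and asthma exacerbation at 48 weeks". The stated adjustment is for BMI and body weight.

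**The concern.** The final stool and blood samples are taken after the exacerbations to which they are related. Patients classed as exacerbators are, in part by definition, those given extra antibiotics or systemic steroids. The Discussion itself relies on an antibiotic being able to change the gut flora. A difference in 48-week change between patients with and without exacerbations may therefore reflect how exacerbations were treated, not a link between the microbiome and asthma.

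This matters because the association is the article's stated way of exploring mechanism. The before-after design is also defended (2.1) on the ground that it avoids baseline diversity between individuals. Pairing removes stable differences between patients. It does not remove an exposure that arises during follow-up and tracks the outcome.

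**Working it through.** The plan gives no figure to reproduce here. The point is one of design logic, followed by an illustration of size.

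**Step 1. The sequence.**
1. First stool at visit 1; first blood at visit 2, when azithromycin starts.
2. Exacerbations occur over 48 weeks. Some are identified by an antibiotic or systemic steroid course, and such courses are permitted.
3. Second stool and blood at visit 7.
4. Change from the first to the second sample is related to the exacerbations in item 2, with no exposure term in the model.

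Exposure to these drugs thus lies between exacerbation and the second sample.

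**Step 2. Expected spurious difference.** Let q be the share of exacerbators given such a course, q0 the same share among exacerbation-free patients, and d the shift per exposed patient in SD of the biomarker change. With no biological link,

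expected difference (exacerbators minus others) = −(q − q0) × d.

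The article gives none of these three values. It allows antibiotics for infections too, so q0 need not be zero, and any q0 above zero shrinks the difference. Because every patient takes azithromycin, d means the extra effect of a further course on top of it.

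**Step 3. Illustration.** N = 44 (2.6), q0 = 0, no biological link, a two-group t-test at two-sided 5%, 4000 simulated datasets per setting. The 90% exacerbating is the article's planning value (2.6); 60%, q and d are assumptions.

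| q | d (SD) | −q × d | False positives, 90% exacerbating* | False positives, 60% exacerbating |
|---|---|---|---|---|
| 0.3 | 0.5 | −0.15 | 6.6% | 7.1% |
| 0.6 | 1.0 | −0.60 | 17.6% | 41.8% |
| 0.9 | 1.0 | −0.90 | 41.4% | 79.1% |

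*Only the 82% to 83% of datasets with at least 3 exacerbation-free patients.

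With d = 0 and 60% exacerbating, the rate is 4.3%, near nominal. The t-test stands in for the planned logistic model, so the table shows direction and range, not a forecast.

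**Step 4. Samples close to an exacerbation.** The article gives no event rate. Assume 1.5 to 2.5 exacerbations per patient-year, evenly spread (Poisson).
- Chance of at least one in the 4 weeks before visit 7: 1 − exp(−1.5 × 4/52) = 0.109, or 4.8 of 44; 1 − exp(−2.5 × 4/52) = 0.175, or 7.7 of 44.
- Not all of these would be treated with the drugs in question. If half were (assumption), 0.5 × 4.8 = 2.4 to 0.5 × 7.7 = 3.85, so about 2 to 4 of 44.
- Exacerbation-free over 48 weeks: exp(−1.5 × 48/52) = 0.25, or 11 of 44; exp(−2.5 × 48/52) = 0.10, or 4.4 of 44. The article's planning value of 90% exacerbating also gives 4.4.

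The comparison group is small, about 4 to 11 patients under these assumptions.

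**The case against.** The case on the other side has real substance.

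- **Not every exacerbation brings exposure.** Events met only by SABA use or an inhaled steroid increase carry no antibiotic or systemic steroid, and exacerbation-free patients may get antibiotics for infections. This stands. The exposure imbalance is a tendency of unknown size, and at the low end of the table the error rate is close to nominal.
- **All patients take daily azithromycin.** This stands too. Only the added effect of a further course matters, and it may be small.
- **The analysis is exploratory, and a limitation is admitted.** The Discussion concedes that exacerbation triggers and other influences on the microbiome may differ before and after treatment. It does not name exacerbation treatment or say how to handle it.
- **An article leaves detail to the full protocol.** A sampling window or medication log may exist there. But the permission, the sampling visits and the covariates are stated positively here, and a sampling window would not add exposure to the stated model.
- **Visit 1 versus visit 2.** The text and Table 1 agree, the interval is not given, and neither sample is meant to follow treatment. The mismatch is minor.

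Two stronger readings are tempting. A reader might infer that the association is bound to appear and that the mechanistic aim is out of reach. The definition has routes without these drugs, the aims are worded as exploration and correlation, and the size cannot be derived from the article, so that does not follow. A reader might also infer that prescribers, knowing that patients take a daily antibiotic, will add fewer courses and so lower the primary endpoint. Nothing in the article supports this. The endpoint is the proportion with any exacerbation, so a withheld course matters only if it would have been the patient's sole qualifying event.

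**Conclusion.** The concern holds for the exploratory analysis of microbiome and biomarker change against exacerbation. As planned, that analysis cannot separate a biological link from the effect of treating exacerbations. The before-after diversity comparison, a secondary endpoint, is touched less directly, since such courses can also affect either stool sample. The primary endpoint is not affected.

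The direction of the exposure imbalance follows from the definitions, provided that courses given for infections do not even it out. Its effect does not follow: it depends on the share treated, the added drug effect and the time from course to sample, none of which is given. The simulated range from 6.6% to 79.1% rests on assumed values and on no exposure among exacerbation-free patients, so it should not be read as an estimate.

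**What to change.** Amend 2.8 as follows. These are changes to analysis and data recording, with no change to clinical management.

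1. **Baseline as predictor.** Add an analysis of baseline microbiome and biomarkers as predictors of later exacerbation. Treatment of on-study exacerbations cannot affect a baseline sample. Courses given before enrolment still can, because every patient had an exacerbation in the previous year, and the report should say so.
2. **Record exposure and test sensitivity.** Record dates and agents of all non-study antibiotic and systemic steroid courses. Add a sensitivity analysis restricted to sample pairs with no such course in the 4 weeks before either sample, borrowing the protocol's own macrolide window. State that this removes exacerbators preferentially. For that reason it should not be the main analysis. Adjustment for cumulative course-days should not be the main analysis either, because it conditions on part of the outcome definition.
3. **Reporting.** Describe change-exacerbation associations as non-directional, and name exacerbation treatment as an alternative explanation.
4. **Sampling, where feasible.** Collect the baseline stool at visit 2 before the first dose, so that it matches the baseline blood.

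Cost: one sample moved to the next visit, medication dates recorded, and a few extra analyses. The sensitivity analysis will have fewer pairs. With perhaps 4 to 11 exacerbation-free patients, all of these analyses will be imprecise.

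### The paired before/after stool comparison cannot separate azithromycin from other permitted antibiotics, and the net bias can mimic or hide an effect

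*Protocol article*

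**What the plan says.** - **Permitted drugs (2.1).** The article states that "corticosteroids and antibiotics other than macrolide antibiotics are allowed to treat exacerbations and/or infections at baseline and during participation in the present study". The permission covers the time before the first stool as well as the time before the second.
- **Exacerbation definition (2.1).** One of the listed criteria of a moderate exacerbation is "administration of antibiotics considering exacerbation of asthma-related symptoms".
- **Entry rule (2.3).** The only antibiotic exclusion is "macrolide antibiotic treatment in the previous 4 weeks". No matching window is given for other classes.
- **Stool sampling (2.5 and Table 1).** Gut microbiome analysis "will be performed at visit 1 and visit 7", that is, at screening and at week 48. No stated rule links sampling to recent antibiotic use.
- **Endpoint and test (2.4, 2.8).** The secondary endpoints include "the diversity indices of the gut microbiome including the Chao 1, Shannon, and Simpson indices". Section 2.8 assigns paired t-tests or McNemar's tests to "the diversity indices of the gut microbiome at pre-treatment and post-treatment as secondary endpoints" and names no covariate.
- **Exploratory models (2.4, 2.8).** Changes in biomarkers, gut species among them, are related to exacerbation at 48 weeks by a "logistic regression model, adjusting BMI and body weight". This is the only adjustment named in the analysis section.

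**The concern.** Section 2.1 defends the single-arm design on the ground that a before/after comparison removes individual diversity at baseline. That is true of differences that stay constant within a person. An antibiotic course taken shortly before one stool and not the other is not constant, and the same section permits it. The Introduction itself lists antibiotics among the interventions that act on the gut microbiome, so the exposure is relevant on the plan's own account.

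Two results are at stake. First, within this trial the paired change is the evidence that azithromycin altered gut diversity, and there is no control arm to show what would have happened otherwise. Second, the trial aims to find microbes that go with fewer exacerbations. A single antibiotic course can count as the exacerbation and also alter the week-48 stool. An association between the two could then reflect the definition of the outcome rather than biology, and adjustment for BMI and body weight does not touch this.

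**Working it through.** The plan gives no antibiotic rate, no expected diversity change and no power for this endpoint, so there is no figure of its own to reproduce. The calculation below only shows how large the problem could be.

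**Inputs**
- n = 44, the required number in 2.6 (the target is 50).
- Two-sided 5% test; true azithromycin effect on diversity set to zero.
- Window of 4 weeks before each stool, borrowed from the macrolide exclusion in 2.3 (assumption).
- Course rate r of 0 to 2 per patient-year before each stool (assumption).
- A course in the window moves that stool's index by 1 SD of the paired change seen in unexposed patients (assumption).

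**Formulas**
- Share exposed before a stool: p = 1 − exp(−4r/52). For r = 0.5, p = 0.038; for r = 1.2, p = 0.088; for r = 2, p = 0.143.
- Expected bias in the mean paired change, in SDs: b = p7 − p1, where p1 and p7 are the shares exposed before visit 1 and visit 7. Positive b means a shift in the direction in which other antibiotics move the index.
- SD of the paired change: s = √(1 + p1(1 − p1) + p7(1 − p7)).
- Rejection probability: noncentral t with 43 degrees of freedom and noncentrality b√44/s, checked by simulating 200,000 trials per row.

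| Courses/year before visit 1 | Courses/year before visit 7 | b (SD) | s | False positives |
|---|---|---|---|---|
| 0.5 | 0.5 | 0 | 1.04 | 5.0% |
| 2 | 2 | 0 | 1.12 | 5.0% |
| 0 | 0.5 | 0.038 | 1.02 | 5.6% to 5.7% |
| 0 | 2 | 0.143 | 1.06 | 13.8% to 14.1% |
| 2 | 1.2 | −0.054 | 1.10 | 6.2% |

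Ranges in the last column are simulation and formula. For scale, the standard error with no other antibiotic is 1/√44 = 0.15 SD.

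**Reading**
- With equal exposure the expected bias is zero. The SD rises by 4% to 12%, which costs precision but produces no false effect.
- The error rate reaches about 14% only when the screening stool is taken to be unexposed.
- In the last row, exposure falls over the trial. False changes in the direction in which other antibiotics act occur in about 1.2% of trials, below the nominal 2.5%, and those in the opposite direction rise to about 5.1%. A real azithromycin effect in the first direction would be partly hidden.

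**Sensitivity.** If the effect of a course outlasts 4 weeks, net exposure could be larger. With a net extra 25% of patients exposed before week 48, the false-positive rate is 12% for a 0.5 SD shift and 32% for 1 SD. The documents do not show whether this applies.

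**Size of the unexposed group.** With equal rates of 0.5 to 2 per year, the share exposed before at least one stool is 1 − exp(−8r/52) = 7% to 26%. That leaves 44 × 0.926 ≈ 41 down to 44 × 0.735 ≈ 32 patients. At an unchanged SD, the standard error grows by √(44/41) = 1.04 to √(44/32) = 1.17.

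**The case against.** A reader might infer that the effect of other antibiotics will be credited to azithromycin. The documents do not support that. The permission in 2.1 covers baseline too. Under 2.2 every patient had an exacerbation in the year before entry, and 2.6 expects the rate to go from 100% to 90%. If exacerbations drive antibiotic use, exposure could be lower before week 48 than before screening, and the bias would then hide an effect. Nor do the documents say that other antibiotics move Chao 1, Shannon or Simpson in the same direction as azithromycin. This part of the objection stands, and the point is therefore stated without a sign.

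The Discussion concedes that other factors affecting the gut microbiome may not be standardized before and after treatment. This is a fair partial disclosure, but it does not name antibiotics and offers no remedy.

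A reader might also say that the plan ignores antibiotic use. That cannot be established. Course dates and sensitivity analyses may sit in the full protocol, case report form or SAP, and antibiotic-treated exacerbations have to be captured for the primary endpoint anyway. What can be said concerns the analysis that the article does state, which is an unadjusted paired test presented as the answer to individual diversity.

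Finally, exposure before week 48 arises after treatment starts and is likely to be commoner in patients who exacerbate. Restricting to unexposed patients selects on a post-treatment variable, and it still does not remove diet, season or corticosteroids. This stands as a reason not to make the restricted analysis the sole basis for attribution.

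**Conclusion.** The concern holds in a limited form. As stated in 2.8, the diversity comparison cannot separate azithromycin from other antibiotics that 2.1 permits, because pairing does not remove a within-person change in exposure and there is no control arm. The bias depends on the net difference in exposure between the two stools, and its sign is open. Under a 1 SD shift, a 4-week window and 0 to 2 courses per patient-year before each stool, the false-positive rate lies between 5% and about 14%. All three inputs are assumptions, so this is a range and not an estimate.

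The second consequence needs no arithmetic: an antibiotic course is both a route to being counted as a moderate exacerbation and a possible cause of a changed stool, so the exploratory association between gut species and exacerbation may arise partly by definition.

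The primary endpoint test is not affected by this point.

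**What to change.** 1. Keep the all-patient paired comparison of the diversity indices as the main analysis.
2. Confirm that start and stop dates of every non-macrolide course are recorded, from at least 4 weeks before visit 1 through visit 7.
3. Prespecify a supportive analysis of the indices, either in patients with no such course in the 4 weeks before either stool, or in all patients with separate terms for exposure before visit 1 and before visit 7. One combined indicator should be avoided, because exposure at the two times acts on the paired change with opposite signs.
4. Apply the same restriction or adjustment to the exploratory models relating microbiome change to exacerbation at 48 weeks.
5. State that a diversity change will be described as consistent with azithromycin only if the two analyses agree, and note that exposure before week 48 is a post-treatment variable.

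**Cost.** A dated concomitant-medication record, if it does not already exist, and a few sentences of analysis text. The restricted analysis rests on about 32 to 41 of 44 patients under the assumed rates, with a standard error about 4% to 17% larger. No treatment, visit or eligibility rule changes. The dates need to be captured prospectively, so this is best settled before the week-48 stools are collected.
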